#### Randomisation

Immediately following the completion of the baseline assessment, participants began the online training task. Participants were automatically randomised to either the intervention or the control training task via a pre-computed randomisation procedure. A permuted block randomisation procedure was utilised [46] whereby participants were allocated to the intervention or control group through the use of a randomly generated number. The permuted blocks were organised in groups of ten, the details of which were not known by investigators involved with the administration of the trial. The use of the permuted block randomisation process ensures that intervention group numbers will be balanced at the end of each block and is thus the recommended process in studies with smaller samples.

Upon finishing this task participants were instructed to complete the online training task once per day for the next 13 days, totalling 14 sessions. They were asked to rate their smoking craving level before and after each training session. Twice per week, participants were sent text reminders to complete the training. All data from the online training task and outcome measures were securely stored on the Deakin University server and linked to an anonymous participant ID number such that only de-identified data were available to researchers. The data was checked for training task performance accuracy and participant adherence to the training protocol by a research assistant who was independent from investigators and not involved in data collection or analyses.

#### Inhibition training task

The intervention is an online GNG training task as developed by Lawrence et al. [36], modified to incorporate images of smoking. The task included nine smoking images (or household items in the control group), nine relaxation images (or household items in the control group) and 18 neutral filler images presented on the left or right of the computer screen (see Fig. 1). Each image was presented for 1250 ms followed by a 1250 ms inter-stimulus interval. Participants were instructed to indicate whether the image is located to the left or the right of the screen using the keys “C” and “M” respectively on their keyboard. On half of the trials, the frame around the picture was bolded and the participants were required to not respond (no-go trials). On the other half of the trials the frame was not bolded (go trials) and the participant were required to respond as quickly as possible. During each training session participants completed 6 training blocks, with each of the 36 images presented once per block. At the end of each block, participants were provided with feedback on their accuracy and mean correct go reaction time and will be encouraged to continue trying to beat their own score. Each training session will last for approximately 10 min. Participants were asked to complete the training at home in a quiet place and preferably, when they experienced cravings for a cigarette.

**Fig. 1 Fig1:**
[figure not shown]
Overview of the “go” and “no-go” trials in the treatment condition of the GNG task. Image source (clockwise from top left) - permission granted: Pixabay [71]; Studio Art/Shutterstock [72]; [name] (Author)

#### Intervention group

The intervention consisted of nine smoking-related images, nine relaxing images.

(i.e. depicting relaxing/enjoyable activities), and 18 neutral filler pictures (e.g. clothing). For the intervention group, the smoking-related pictures were always “no-go” trials and the non-smoking pictures were always “go” trials. The neutral pictures were equally “go” and “no-go” trials (see Fig. 1). The neutral filler pictures were incorporated to prevent participants from easily identifying the associative rules of the task and to ensure the task remains challenging and engaging.

#### Control group

In the control group, participants complete a similar task to the smoking intervention group except that randomly presented 18 images of household objects replace the 18 smoking and relaxation images. The household images were presented equally as “go” and “nogo” trials.

#### Post-intervention (T2)

At the completion of the two-week intervention period, participants are contacted via phone by a researcher naïve to the group randomisation (i.e. a different researcher to the one who conducted the baseline interview). They receive a text message reminder 24-h prior to confirm the time of the phone call. During these phone interviews, participants are asked to provide details about their use of cigarettes and nicotine replacement therapies or anti-craving medications over the previous 2 weeks. At the conclusion of this interview, participants are emailed a link to complete the same battery of questionnaires, ratings of their craving, motivation and self-efficacy and SST (completed last) as completed at baseline (T1).

#### One-month and three-months follow-up (T3 and T4)

Follow-up at 1 month (T3) and 3 months (T4) are conducted in the same manner as T2. The two follow-up time points are identical with the exception that the SST was not completed at T3 only in T4 to reduce participant burden. At the completion of each time point, participants were mailed a $20 gift card. At the conclusion of the data collection period, participants in the control group are offered the opportunity to complete the smoking-related response inhibition training.

## Measures

This study used information from a face-to-face interview session (T1) and phone interviews (T2, T3 and T4), in addition to self-report questionnaires, a cognitive task and a stimulus evaluation test. A list of measures used at each assessment point is provided in Table 1. Demographic information, such as age, gender, socioeconomic status and number of years of smoking, were collected at baseline.

### Researcher-administered measures

#### *Timeline Follow-Back (TLFB)* [47, 48]

The TLFB is a calendar-based assessment of daily cigarette use for periods of time ranging from 1 to 12 months prior to assessment. Initially developed to assess alcohol consumption, the TLFB has since been utilised to assess a variety of substance use inclusive of cigarette use [47]. Memory aids are used to enhance recall of certain time-periods in order to retrospectively estimate number of cigarettes used for each date. The cigarette TLFB has shown high test-retest reliability and temporal stability across both clinical and non-clinical participants [47].

### Self-report measures

#### *Fagerström Test for Nicotine Dependence (FTND)* [49]

The FTND is a six-item self-report questionnaire of nicotine dependence. Dichotomous items (yes or no) are scored as 0–1, and options for categorical items are scored 0–3. The FTND has a maximum score of 10, with higher scores indicating greater nicotine dependence. The FTND demonstrates moderate internal consistency (α = .61) and has been validated in smokers from the general population [48] and in a clinical sample [50].

#### Craving for cigarettes

A one-item question utilising a 100 mm slider scale measures craving from “not at all” to “extremely”. Participants respond to the question “How much are you currently craving a cigarette”. A slider bar is presented at the left end of the scale and participants will click and drag the bar along the scale to indicate their response. It has been found that a single measure of craving is just as reliable and sensitive as self-report questionnaires for measuring craving for smoking [51, 52]. Slider scales are considered to be an engaging type of interface [53] and are regarded as a psychometrically acceptable measurement [54].

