### Secondary hypotheses

Smokers who received smoking-related response inhibition training (INST program) would report significantly less craving for cigarettes compared to smokers in the active control condition at the end of the intervention and 1 month and 3 months post-intervention.Smokers who received smoking-related response inhibition training (INST program) would report significantly lower levels of nicotine dependence compared to smokers in the active control condition at the end of the intervention and 1 month and 3 months post-intervention.

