#### Ratings of motivation and self-efficacy

Participants are asked to rate their motivation (“currently, how motivated are you to reduce or quit smoking?”) and self-efficacy (“currently, how confident are you in your ability to quit or reduce smoking?”) on slider scales. The scale is a 100 mm line with the left anchor labelled “not at all” and the right anchor labelled “extremely”. Similar to the craving slider scale, participants indicate their response by clicking and dragging the slider bar along the scale.

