#### Stimulus evaluation test (ratings of likeability of smoking and relaxing images)

Slider scales are used for the likeability ratings of the smoking and relaxing images used in the inhibition training task (INST). Participants are presented with the question, “how much would you like to do this activity right now?” and rate the images from “not at all” to “extremely”. The slider bar is presented in the middle of the scale and participants click and drag the slider bar to indicate their response.

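### The craving slider rests on a valid answer, so unless the survey forces or logs a click, a skipped rating and a true zero look alike

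*Protocol article*

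**What the plan says.** All references are to the protocol article.

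- **Craving for cigarettes.** One item on a 100 mm slider running from 'not at all' to 'extremely'. The start position and the response are both stated: "A slider bar is presented at the left end of the scale and participants will click and drag the bar along the scale".
- **Ratings of motivation and self-efficacy.** This section says which label is on the left: "The scale is a 100 mm line with the left anchor labelled “not at all". It likens the response to the craving item: "Similar to the craving slider scale, participants indicate their response by clicking and dragging the slider bar along the scale". It does not say where its own handle starts.
- **Stimulus evaluation test.** Here the start differs: "The slider bar is presented in the middle of the scale".
- **Secondary hypotheses.** Lower craving is success. The INST group "would report significantly less craving for cigarettes compared to smokers in the active control condition" at the end of the intervention and at 1 and 3 months.
- **Setting.** Baseline ratings are taken at a face-to-face interview. At T2, after the phone call, "participants are emailed a link to complete the same battery of questionnaires, ratings of their craving, motivation and self-efficacy"; T3 and T4 run in the same manner. Under Randomisation, craving is also rated before and after each training session, and 13 of the 14 sessions are done at home.
- **Analysis plan.** Craving goes into a mixed-design ANOVA of group by time. Missing data are examined first and, if appropriate, multiply imputed.

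The article does not say whether a click is required, whether movement is logged, or how an untouched handle is stored.

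**The concern.** The handle sits on a valid answer before the participant does anything. On the craving item that answer is, by analogy with the sister sliders, no craving at all. Someone with no craving has nowhere to drag the handle. As described, that person and someone who clicked past the item leave the same record.

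The problem lies in a stated display choice, not in missing detail. If the platform kept no trace of interaction, a later coding rule cannot recover the distinction. Stored as 0, a skip enters as complete absence of craving, and the planned missing-value analysis does not see it. Stored as missing, a true zero left in place is lost because of its own value, and the answers from which imputation would learn contain too few zeros.

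Baseline is taken in person and later ratings are not, so any click-through would arise mainly after baseline. The outcome at stake is one of the two secondary hypotheses. The picture ratings behind the devaluation mediator have a weaker form of the problem: an untouched handle there reads as middling liking and pulls ratings towards the midpoint.

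**Working it through.** The plan gives no figure to reproduce. The check has a reading part and an illustration.

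**Reading.** The handle starts at the left (Craving for cigarettes). Left is 'not at all' on the sister sliders (Ratings of motivation and self-efficacy). The craving anchors are listed in the same order. The resting position is therefore very probably zero craving. The only response described is a drag, so a true zero has no action of its own.

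**Illustration. Every rate is an assumption; none is in the documents.**
- pz: share with true zero craving, 20% in INST and 10% in control; null case 10% in both.
- Mean craving of the others: 50 mm.
- s: share who skip the item, unrelated to craving.
- g: share of true zeros who leave the handle in place.

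True mean = (1 - pz) × 50, so 40.0 v 45.0, a difference of -5.0.

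*Untouched stored as 0:* mean = (1 - s)(1 - pz) × 50.

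| Skipping, INST / control | Arm means | Difference (true -5.0) |
|---|---|---|
| 5% / 5% | 38.0 v 42.75 | -4.75 |
| 10% / 10% | 36.0 v 40.5 | -4.5 |
| 10% / 5% | 36.0 v 42.75 | -6.75 |
| 5% / 10% | 38.0 v 40.5 | -2.5 |

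In the null case (45.0 in both arms), equal skipping gives 0. Skipping of 10% / 5% gives 40.5 - 42.75 = -2.25, and the reverse gives +2.25.

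*Untouched stored as missing:* mean among those who moved the handle = (1 - pz) × 50 / (1 - pz × g).
- g = 0.5: 40/0.90 = 44.4 v 45/0.95 = 47.4, difference -2.9.
- g = 1: 40/0.80 = 50 v 45/0.90 = 50, difference 0.
- Null case: 0 for any g that is equal in the arms.

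These are means before imputation.

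*Click required or logged:* s = 0 and g = 0, and both codings return -5.0, or 0 in the null case.

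**Precision when skips are stored as 0 equally in both arms.** Assume instead means of 50 and 37.5 mm and SD 25, so d = 0.50. Mixing in a share u of zeros gives:
- u = 5%: 11.9/26.2 = 0.45
- u = 10%: 11.3/27.2 = 0.41
- u = 15%: 10.6/27.9 = 0.38

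From (0.5/d)², using unrounded d, the sample-size ratios are 1.22, 1.46 and 1.73. Ordinary visible non-response would already cost 1/(1 - u) = 1.05, 1.11 and 1.18. The part due to the coding is the quotient: about 16%, 31% and 47%.

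**The case against.** The strongest reply is that the harm depends on the survey build. A forced response, a registered click at zero or an interaction log would remove it, and a condensed article need not describe such settings. This stands. The point holds only if none of these exists, and the silence itself is not a fault. What remains is that the format as stated creates the ambiguity and a better format is available at little cost.

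Several stronger readings are tempting, and the documents do not support them:

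- **Either coding always biases the result.** Storing as 0 matters only if items are skipped. Storing as missing matters only if true zeros leave the handle.
- **The artefact favours INST.** With equal skipping a real effect is attenuated and none is created under the null. A false benefit needs more skipping in INST. Nothing suggests that: the tasks are similar, participants are described as likely blind, and reminders and gift cards are not distinguished by arm.
- **Zero is the true answer of many quitters.** No such rate is given. The item asks about craving at the moment, so a smoker who has just smoked could also answer zero.
- **All sliders share the fault.** No start position is given for motivation and self-efficacy. The mid-scale start of the picture ratings does not coincide with a favourable answer.

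The planned multiple imputation, which uses baseline covariates and outcome data, may recover part of what is lost if untouched scales are stored as missing.

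**Conclusion.** The concern holds in conditional form. The described craving slider confounds non-response with zero craving unless the survey forces or logs a click. Stored as 0, untouched sliders attenuate a real arm difference when skipping is equal and distort it, in either direction, only when skipping differs by arm. Stored as missing, they remove true zeros, a loss that depends on the unseen value.

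The documents give no rate of skipping or of zero craving, so the size cannot be derived. The figures above show a range under assumptions: a true -5.0 mm difference is seen as anything from -6.75 to -2.5 when stored as 0, and -2.9 or 0 when stored as missing with half or all true zeros untouched. A reader might infer that the craving data are already compromised or that the trial leans towards INST; neither follows. The point concerns a secondary outcome and does not touch the primary smoking outcomes. It is worth acting on because the remedy is cheap.

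**What to change.** **Ratings still to be collected.** Show the craving scale with no handle until the participant clicks on the line. Accept a click at 'not at all' as an answer, store an answered flag, and code only unclicked scales as missing. As a lesser point, do the same for the picture ratings. If the build already forces or logs a click, a sentence saying so is enough.

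**Ratings already collected.** Use the platform's interaction or timing records where they exist. Where they do not, and untouched scales were stored as 0, keep exact zeros in the main craving analysis and add one sensitivity analysis with exact zeros set to missing. Present it as a bound. If skipping is unrelated to craving, the pair brackets each arm's mean but not necessarily the difference: with 5% skipping in both arms it gives -4.75 and 0 against a true -5.0. Do not choose which zeros to delete by abstinence on the Timeline Follow-Back. That conditions on a post-randomisation primary outcome and discards true zeros from people still smoking.

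**Cost.** A display setting, one stored flag and one extra analysis, with no added burden on participants. The drawback is a small change of format between baseline and later ratings for participants already enrolled. It touches the time factor of the ANOVA but is the same in both arms, and randomisation in blocks of ten keeps the arms balanced over calendar time. The date of the change should be recorded.

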#### *Depression, Anxiety and Stress Scale (DASS-21)* [55]

The DASS-21 is a 21-item measure consisting of three subscales: depression, anxiety, and stress. Participants are asked to use a four-point Likert scale to rate the extent to which they have experienced the state described over the past week. The DASS has excellent internal consistency for the total scale (α = .97), and each subscale (Depression = .96; Anxiety = .92; Stress = .95) has high test-retest reliability and acceptable construct and convergent validity [56].

#### *Alcohol Use Disorders Identification Test (AUDIT)* [57]

The AUDIT is a 10-item measure of alcohol problems. Questions relate to frequency and quantity of consumption, and alcohol-related problems. Participants are asked to rate items from 0 to 4 and can receive a maximum possible score of 40, with higher scores indicative of more hazardous drinking, AUDIT is highly reliable and valid for use across a range of populations [58].

#### *Barratt Impulsiveness Scale (BIS-11)* [59]

The BIS-11 is a 30-item questionnaire assessing trait impulsivity. Each item is scored on a four-point Likert scale that ranges from “rarely/never” to “almost always”. Scores are summed to yield an overall total score ranging from 30 to 120, with higher scores indicating greater trait impulsivity. The BIS-11 also provides scores on three subscales: attentional impulsiveness, motor impulsiveness, and non-planning impulsiveness. The BIS-11 is widely used in research and clinical contexts and has been shown to demonstrate good reliability [59, 60].

#### Ratings of motivation and self-efficacy

Participants are asked to rate their motivation (“currently, how motivated are you to reduce or quit smoking?”) and self-efficacy (“currently, how confident are you in your ability to quit or reduce smoking?”) on slider scales. The scale is a 100 mm line with the left anchor labelled “not at all” and the right anchor labelled “extremely”. Similar to the craving slider scale, participants indicate their response by clicking and dragging the slider bar along the scale.

#### Stimulus evaluation test (ratings of likeability of smoking and relaxing images)

Slider scales are used for the likeability ratings of the smoking and relaxing images used in the inhibition training task (INST). Participants are presented with the question, “how much would you like to do this activity right now?” and rate the images from “not at all” to “extremely”. The slider bar is presented in the middle of the scale and participants click and drag the slider bar to indicate their response.

### Cognitive task

#### Stop Signal Task (SST) [32, 61, 62]

A smoking-specific version of the SST [30, 32, 61–63] is utilised. The SST contains images of smoking-related stimuli that are different images from those used in the intervention task. Participants are presented with a fixation cross in the centre of a screen on a white background for 500 ms. A smoking-related image (go-stimulus) then appears for 1000 ms, followed by a blank white screen for 1000 ms (inter-stimulus interval). The 16 images used in the SST are comprised of 8 pairs of images, where one image of the pair is a cigarette pointing to the left, and the second image is its mirror image pointing to the right. As such, the presentation of stimuli pointing left or right will be equally balanced. Each of the 16 images is presented a total of 12 times.

Participants are instructed to indicate whether the cigarette is pointing left or right by pressing the computer keys “C” or “M” respectively (Fig. 2). The stop signal is a pair of red lines across the image and will appear on 25% of trials. It appears at a short delay (Stop Signal Delay or SSD) after the onset of the go stimulus and stays on screen until the inter-stimulus interval. Participants are instructed to respond as quickly as possible but to not respond when the red lines appear. This delay between the onset of the go signal and the stop signal begins at 250 ms on the first stop trial, and then adjusted by 50 ms in a staircase manner. Successful inhibition on stop trials results in the SSD increasing for the next stop trial, while unsuccessful inhibition, where the participant responds on a stop trial, will shorten this delay by 50 ms. The SST consists of one practice block of 10 trials followed by the experimental block of 192 trials. The SSD will be used to calculate the stop signal reaction time (SSRT) as a measure of response inhibition and the reaction time on go trials will be a measure of behavioural impulsivity [62].

**Fig. 2 Fig2:**
[figure not shown]
Overview of the “go” and “stop” trials in the Stop Signal Task illustrating correct responding. Image source - permission granted: Khamiranon D/Shutterstock [73]

### Analysis plan

All participants will be included in the intent-to-treat analyses for the primary and secondary hypotheses. If relevant, per protocol analysis will include those who complete at least four sessions of the training (as per Lawrence et al. [36]) and achieve a training accuracy of at least 70%. SST data will be included for those who yield an accuracy of 40–60% on stop trials and at least 70% on go trials. Prior to analyses, all variables will be examined through IBM Statistical Package for Social Sciences (SPSS Version 25) for accuracy of data entry, missing values and fit between their distributions and the assumptions of multivariate analysis. Any violations will be addressed as per standard protocols [64].

Missing data will be managed using SPSS. First, a missing value analysis will be conducted to determine the percentage and pattern of missing data. If missing data are found to relate to a measured participant variable, those variables will be included as covariates in the analyses. If appropriate, multiple imputation will be used to replace missing values and the imputation model will include baseline covariates and outcome data. Missing data will be imputed using the Markov Chain Monte Carlo method or the Monotone method, contingent upon the pattern of missing data. A minimum of five imputed datasets will be produced [65]; however, depending on the percentage of missing data, a minimum of 20 imputed datasets may be required [66]. Wherever possible, results from the complete case analysis will be compared with results based on imputed data. If there are important differences, explanations will be offered.

The primary and secondary hypotheses will be analysed using separate mixed-design ANOVAs and a Chi-square analysis for the binary outcome. Depending on the rate of smoking abstinence at follow up the outcome variable will be calculated as either binary (smoking abstinence: yes/no) or percent days abstinence if Chi-square analysis is contraindicated due to low numbers in each cell. For all other mixed design ANOVAs group (i.e., intervention or control) will be included as the between-subjects factor and time (survey time points) is the within-subjects factor. For the smoking reduction primary hypothesis, the repeated-measures factor will be the average number of cigarettes smoked per day at each timepoint (i.e., baseline, post-intervention, 1 month and 3 months post intervention). For the secondary hypotheses, the repeated-measures factor will be craving or nicotine dependence at each timepoint. The predictor hypotheses will be examined using separate moderated regression analyses, with group as the predictor variable, impulsivity and dose as the moderator variable and change in smoking as the dependent variable.

The two mediation hypotheses will be analysed utilising a linear mixed model approach to examine whether the effects of INST training on level of smoking will be mediated by devaluation of smoking stimuli or an independent measure of response inhibition (SSRT).

The exploratory questions related to self-confidence and motivation will be examined using a separate mixed-design ANOVA, with group included as the between subjects factor and self-confidence and motivation at each timepoint included as the repeated-measures factor.

Repeated measures ANOVAs will be performed on “go” reaction times and “no-go” accuracy to examine stimulus-specific learning effects (100% stimuli vs. 50% stimuli) over time (first vs. fourth training session as per the analysis by Lawrence and colleagues to allow comparability). Evidence of learning across the two time points will be indicated by faster reaction time on 100% go stimuli and fewer errors on 100% no-go stimuli. Any further exploratory analyses will be labelled as such in the publication.

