### Primary hypotheses

Smokers who received smoking-related response inhibition training (INST program) would report significantly higher cessation rates compared to those in the active control condition at the end of the intervention, 1 month and 3 months post-intervention.Smokers who received smoking-related response inhibition training (INST program) would report significantly less cigarette consumption compared to smokers in the active control condition at the end of the intervention, 1 month and 3 months post-intervention.

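### For cigarettes per day, craving and nicotine dependence, baseline is a level of the ANOVA time factor instead of a covariate, so the test is valid but avoidably weak and poorly matched to the follow-up hypotheses

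*Protocol article*

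**What the plan says.** The Analysis plan section of the protocol article sets the method: "The primary and secondary hypotheses will be analysed using separate mixed-design ANOVAs and a Chi-square analysis for the binary outcome". In the ANOVAs, group "will be included as the between-subjects factor and time (survey time points) is the within-subjects factor". For smoking reduction, the repeated measure is "the average number of cigarettes smoked per day at each timepoint (i.e., baseline, post-intervention, 1 month and 3 months post intervention"; that makes four levels, the first of them before treatment. For the other two outcomes it says: "For the secondary hypotheses, the repeated-measures factor will be craving or nicotine dependence at each timepoint". Table 1 schedules the smoking calendar interview, craving and FTND at all four assessments, T1 to T4.

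The Primary hypotheses section predicts that the intervention arm "would report significantly less cigarette consumption compared to smokers in the active control condition at the end of the intervention, 1 month and 3 months" after the intervention. The Secondary hypotheses section names the same three follow-ups for craving and dependence.

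On the analysis set, the Analysis plan says: "All participants will be included in the intent-to-treat analyses for the primary and secondary hypotheses". It adds multiple imputation where appropriate, with complete-case results as a comparison. The Power analysis section says that the trial was powered on smoking reduction.

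**The concern.** A two-arm, four-level ANOVA offers two tests that involve group, and neither fits a hypothesis about differences "at the end of the intervention, 1 month and 3 months post-intervention".

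- **Group main effect.** It compares the arms averaged over all four levels. Randomisation makes the expected baseline difference zero, so that level adds noise and no signal.
- **Group-by-time interaction.** It asks whether the arm difference changes anywhere across the four levels, with 3 degrees of freedom. A significant result does not say at which follow-up the arms differ.

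The article does not say which of the two decides the hypothesis. At stake are the power for the outcome that sized the trial and a clear answer to the question it poses. The baseline value that would sharpen the comparison is already collected, but it is used as an outcome.

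**Working it through.** **The plan's own figure.** The Power analysis section gives a total of 92 for d of about 0.50, alpha 0.05 and power 0.80. A two-sample t test with these inputs needs 128 two-sided or 102 one-sided, so 92 is not reproduced that way. It can be reached only with inputs the article does not state: for example, ANCOVA at one time point with a baseline correlation of 0.53 gives 128 × (1 − 0.53²) = 92. The article says only that linear techniques were assumed, so this mismatch alone does not show that 92 is wrong. It also does not fix a correlation for the check below.

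**Inputs.**
- From the protocol: target 150, 25% loss to follow-up, d = 0.50, alpha 0.05. 150 × 0.75 = 112.5, taken as 112, or n = 56 per arm.
- Assumed: equal arms (blocks of ten, balanced), two-sided tests, unit variance, equal correlation ρ between any two visits, and ρ = 0.3, 0.5 or 0.7.
- Assumed effect profile over T1 to T4: (0, 0.5, 0.5, 0.5).

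**Shrinkage of the main effect.** (0 + 3 × 0.5)/4 = 0.375, which is three quarters of 0.50.

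**Noncentrality λ, with n/2 = 28.**
- Interaction: the deviations from 0.375 have sum of squares 0.375² + 3 × 0.125² = 0.1875. λ = 28 × 0.1875/(1 − ρ) = 5.25/(1 − ρ); df 3 and 330.
- Main effect over four levels: λ = 28 × 4 × 0.375²/(1 + 3ρ) = 15.75/(1 + 3ρ); df 1 and 110.
- Mean of the three follow-ups, adjusted for baseline: λ = 28 × 0.5²/[(1 + 2ρ)/3 − ρ²]; df 1 and 109.
- One follow-up, adjusted for baseline: λ = 28 × 0.5²/(1 − ρ²); df 1 and 109.

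Power comes from the noncentral F distribution (λ in brackets):

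| ρ | Interaction | Main effect | Adjusted follow-up mean | Adjusted, one follow-up |
|---|---|---|---|---|
| 0.3 | 62% (7.50) | 81% (8.29) | 98% (15.79) | 78% (7.69) |
| 0.5 | 78% (10.50) | 70% (6.30) | 98% (16.80) | 86% (9.33) |
| 0.7 | 95% (17.50) | 61% (5.08) | over 99% (22.58) | 96% (13.73) |

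In each row the λ of the adjusted mean is the sum of the two ANOVA values (for example 10.50 + 6.30 = 16.80). For a constant effect, the ANOVA divides between two tests what the adjusted mean collects in one 1-df test.

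**Timing.** Take an effect at 3 months only, profile (0, 0, 0, 0.5). The mean is 0.125 and the sum of squares is 3 × 0.125² + 0.375² = 0.1875, the same as before. The interaction therefore has the same power as under a constant effect and cannot tell the two patterns apart.

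**Where the gain fails.** Under that late-only profile, the adjusted mean has 26/27/35% power against 62/78/95% for the interaction. Under a fading profile (0.5, 0.33, 0.17) it has 75/77/88%, against 48/63/86% for the interaction and 48/38/32% for the main effect.

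**The case against.** The strongest reply is that the planned test is sound. In a randomised trial, group-by-time with baseline as a level is a valid test of differential change; nothing here shows bias or an inflated type I error. Direction can be read from the group means, and follow-up contrasts after an omnibus test are detail that a condensed article may leave to a fuller plan. That stands, and it limits the point to efficiency and fit. It does not remove the point, because the article itself fixes baseline as an outcome level.

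The second reply is that the large gain belongs to the average over follow-ups, which is no more time-specific than the omnibus test and relies on a sustained effect. That also stands. A reader might infer a large gain at each follow-up, but the figures do not support it. One adjusted contrast has 78/86/96% against 62/78/95% for the interaction. With a Bonferroni split over three visits (alpha 0.05/3, same λ) it has 63/73/90%, so most of that advantage disappears or reverses. Power at one visit is not the chance of a finding at any of the three, but no large per-visit gain is shown.

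A reader might also infer that the ANOVA requires complete data, so that about 38 of 150 (25%) drop out of it. The article does not say so. It includes all participants in the intent-to-treat analyses, plans multiple imputation using baseline and outcome data, and gives complete cases only a comparison role. Imputation is conditional and no rule is given for when it applies, but that is detail commonly left to a fuller plan.

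**Conclusion.** The point holds for cigarettes per day, craving and FTND. Baseline enters as one of four outcome levels without adjustment, and the resulting tests are valid but avoidably weak and do not line up with hypotheses stated at three follow-ups. For a constant d = 0.50 in 112 participants, the adjusted follow-up mean has 98% to over 99% power, against 62 to 95% for the interaction and 61 to 81% for the main effect over ρ of 0.3 to 0.7. This rests on an assumed correlation, compound symmetry and a sustained effect. The advantage shrinks if the effect fades and reverses if it appears only at 3 months.

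It would be tempting to apply this to both primary outcomes. The documents do not support that: binary cessation is tested by chi-square.

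**What to change.** For cigarettes per day, craving and FTND, replace the four-level ANOVA with a linear mixed model that has T2, T3 and T4 as outcomes, the baseline value as covariate, and group, time and group-by-time as terms.

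- Name one primary contrast in advance. The average follow-up difference is one option and suits a sustained effect. If a late effect is what matters, a single named visit suits better.
- Report the group contrast with a 95% confidence interval at each of the three follow-ups, either as supporting results or under a stated multiplicity rule.
- Keep the planned multiple imputation for participants with no follow-up. The mixed model alone uses only those with at least one follow-up value, so imputation is needed to include everyone randomised.
- Leave the chi-square analysis of cessation outside this change.

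The cost is wording in the analysis plan. Table 1 already schedules all three outcomes at T1 to T4, and the article already plans a linear mixed model for the mediation hypotheses.
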